4.2 Exclusion Criteria

- - 1. Inability to complete written, informed consent.
    2. Incarceration at the time of any screening or main study visit.
    3. Diagnosed vascular disease (history of angina pectoris, coronary disease, peripheral vascular disease, cerebrovascular disease, aortic aneurysm, or otherwise known atherosclerotic disease).
    4. Diagnosed disease or process, besides HIV infection, associated with increased systemic inflammation (including, but not limited to, systemic lupus erythematosis, inflammatory bowel diseases, other collagen vascular diseases).

Note: Hepatitis B or C co-infections are NOT exclusionary

- - 1. History of bleeding diathesis, gastrointestinal ulceration or bleeding, cerebrovascular aneurysm or bleeding, or retinal hemorrhage.
    2. Known or suspected malignancy requiring systemic treatment within six months of screening.
    3. History of ADA-defined diabetes mellitus [134]

Note: History of gestational diabetes is not exclusionary if the potential subject does not have current ADA-defined diabetes.

- - 1. History of migraine headaches.
    2. History of Raynaud’s phenomenon.
    3. History of cardiac arrhythmias or cardiomyopathy.
    4. History of hypothyroidism or hyperthyroidism, even if treated.
    5. Known allergy or intolerance to pentoxifylline or other methylxanthines (e.g. theophylline, caffeine, theobromine).

Note: Use of caffeinated products, except on the mornings of the study visits, is not exclusionary.

- - 1. Known allergy or intolerance to nitroglycerin.
    2. History of carotid bruits.
    3. Creatinine clearance < 50mL/min (using the Cockcroft-Gault equation, see Appendix 1) using a serum creatinine level measured within 28 days prior to screening or at screening.
    4. Hemoglobin < 9.0mg/dL within 28 days of screening or at screening.
    5. Alanine aminotransferase (ALT) level or aspartate aminotransferase (AST) > 3 times ULN within 28 days of screening or at screening.
    6. Total bilirubin > 2.5 times ULN within 28 days prior to screening or at screening.
    7. Fever, defined as T ≥ 38.0C within 48 hours prior to screening.

Note: Fever within 48 hours prior to each main study visit will require postponement of that study visit until the patient has defervesced (T < 38.0C) for at least 48 hours; fevers continuing past the allowed study visit timeframe will result in study discontinuation.

- - 1. Therapy for acute infection or other serious medical illnesses within 14 days prior to screening.

Note: Therapy for acute infection or other serious medical illnesses that overlaps with a main study visit will result in postponement of that study visit until the course of therapy is completed; postponement outside of the allowed study visit timeframe will result in study discontinuation.

- - 1. Pregnancy or breastfeeding during the course of the study.
    2. Hypotension, defined as systolic blood pressure < 90mmHg, at time of screening.

Note: Hypotension noted prior to brachial artery reactivity testing on each main study visit will result in study visit postponement of at least one day until systolic pressure is ≥ 90mmHg the morning of brachial reactivity testing; postponement outside of the allowed study visit timeframe will result in study discontinuation.

- - 1. Hypertension, defined as the receipt of any antihypertensive medication within 28 days prior to screening or systolic blood pressure > 160mmHg at screening.
    2. Receipt of anti-inflammatory agents (including, but not limited to, plaquenil, infliximab, etanercept, mycophenylate mofetil, sirolimus, tacrolimus, cyclosporine, pentoxifylline, thalidomide) within 28 days of screening.
    3. Receipt of investigational agents, cytotoxic chemotherapy, systemic or topical glucocorticoids (of any dose and including inhaled or nasal steroids), or anabolic steroids within 28 days of screening.

Note: Physiologic testosterone replacement therapy is not exclusionary.

- - 1. Receipt of lipid-lowering drugs (including prescription or over the counter ‘fish oil’ or omega-3 fatty acid supplements), aspirin, other NSAIDS, acetazolamide, anticoagulants, anticonvulsants, or thyroid replacements within 28 days prior to screening.
    2. Use of sildenafil, vardenafil, or tadalafil within 72 hours (before or after) of each main study visit.
    3. Active drug or alcohol use or dependence that, in the opinion of the investigator, would interfere with adherence to study requirements.

If subjects are excluded due to the above criteria, they may be approached again in the future or have their study visit rescheduled within the allowable timeframe if these criteria are no longer applicable. Co-enrollment into other studies will be permitted provided no drugs prohibited on this study will be given in the other study/ies and that the required blood draws do not exceed safe limits when combined with those for this study.

We are specifically excluding subjects with diabetes, hypertension, and dyslipidemia requiring therapy at screening in these two studies in order to better evaluate the role of HIV as the primary determinant of endothelial dysfunction. However, we will not discontinue study participation if these criteria develop during the course of these trials for two reasons. First, this would limit generalizability as the development of diabetes, hypertension, and severe dyslipidemia with antiretroviral therapy is common in the HIV-infected population. Second, it is possible that reduction of inflammation by PTX may theoretically prevent insulin resistance, hypertension, and hypertriglyceridemia, which are important endpoints to capture in these trials.

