6.3.8.11 Laboratory Evaluations

All screening and main study visit laboratory evaluations performed as part of this study must be present in source documentation. At entry, record all laboratory values on CRFs. For post-entry assessments, record on CRFs all Grade ≥ 2 laboratory toxicities and any laboratory toxicities that led to a change in pentoxifylline dosing regardless of grade. In addition, record on CRFs all values for hemoglobin, serum creatinine/calculated creatinine clearance, liver function tests, urine analysis, urine pregnancy tests, hepatitis B and C serologies, CD4/CD8 cell counts, and HIV-1 RNA levels. Refer to the Division of AIDS Table for Grading Adult Adverse Experiences on the Regulatory Compliance Center Web page: <http://rcc.tech-res-intl.com/>

Screening visit and main study visit safety blood and urine laboratories will be sent to the Indiana University clinical laboratory for immediate processing and analysis; results will be entered on CRFs and forwarded to the Biostatistical Division for electronic storage. Frozen plasma, serum, and urine specimens for future use will be batch analyzed by the IU clinical laboratory or by Searchlight/Endogen Laboratories; these data will be electronically forwarded to the Biostatistical Division. Serum, plasma, and urine specimens will be processed, stored, and shipped to the Data Coordinating Center for the RFA funding this trial. Brachial ultrasound results will be entered on CRFs and sent to the Biostatistical Division. Computer labels will be generated and affixed to the appropriate specimen containers or brachial ultrasound discs and will include the specimen number, subject number, specimen date, and primary specimen type. Labels must be affixed prior to freezing the vials. Specimen collection, processing, and storage instructions are listed under section 6.3.8.12.

NOTE: The peripheral IV heplock used for both drawing blood samples and for infusion of fluids if necessary during the BART procedure should be placed on an extremity other than the arm used for the brachial artery measurements.

Hematology

- Hemoglobin
- White blood cell count (WBC)
- Differential WBC
- Absolute neutrophil count (ANC)
- Platelets

Liver function tests

- ALT (SGPT)
- AST (SGOT)
- Total bilirubin

Blood Chemistries

- Serum creatinine/estimated creatinine clearance
- Serum glucose, potassium
- Hepatitis B surface antigen, hepatitis B surface antibody, hepatitis B core IgM antibody
- Hepatitis C antibody

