7.3 Pentoxifylline (PTX)

7.3.1 Drop in Hemoglobin/Bleeding Episode

Subjects must be educated about the possible occurrence of anemia and bleeding, including abdominal pain, hematochezia, melena, and sudden onset headache. If these symptoms/signs occur, then a hemoglobin level must be checked. A 2gm/dL or greater drop from baseline in hemoglobin or bleeding episode from any site will result in permanent discontinuation of PTX. However, if the primary investigator or primary caregiver has compelling evidence that the drop in hemoglobin or bleeding episode is NOT due to PTX (e.g. trauma), dosing may continue with no more than a one week hiatus at the discretion of the primary investigator or primary caregiver. Rescheduling of a main study visit, if necessary, will be at the discretion of the primary investigator.

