10.3.2 Protection Against Risk

10.3.2.1 Confidentiality. To minimize the risk to subject confidentiality, patient identifiers will be removed once his or her data is abstracted and recorded, and only the random study identification number (generated when consent is provided) will be used. All hardcopy study data will be kept in a secured and locked file cabinet. All electronic data will be kept in a password-protected computer database. The only link between patient identifiers and the randomized study identification number will be kept in separate files. Identifiers will never be used in the analysis or presentation of study results.

10.3.2.2 Blood draws. The risks of blood drawing will be minimized by having only experienced medical personnel perform this procedure. The amount of blood that will be drawn falls well within safety standards for blood donation.

10.3.2.3 Pentoxifylline. Our pilot data and safety results from the literature suggest that PTX is very well-tolerated, so we do not expect any serious adverse events from use of this agent. However, to minimize potential risks with this drug, the eligibility criteria will reduce the potential adverse events associated with this drug by excluding those at higher risk. Adverse events will be monitored for closely. Safety laboratories (complete blood cell counts including platelet counts, chemistries, renal and liver function tests) will be obtained at each main study visit or upon development of symptoms. Grade III or IV abnormalities (defined using the Division of AIDS Table for Grading Adult Adverse Experiences) will prompt immediate discontinuation of the drug. Pregnant and breastfeeding women will be excluded. Women of reproductive age will be asked to use two forms of contraception during the clinical trials.

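### The only hemoglobin eligibility criterion (Section 4.2) is printed in mg/dL, while the on-study hemoglobin rule (Section 7.3.1) is in gm/dL; read literally, the exclusion removes no one

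*Combined protocol and SAP*

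**What the plan says.** Section 4.2 lists, among the laboratory exclusions, "Hemoglobin < 9.0mg/dL within 28 days of screening or at screening". It is the only eligibility criterion based on a hemoglobin value.

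Section 7.3.1, on adverse event management, uses a different unit for the same analyte: "A 2gm/dL or greater drop from baseline in hemoglobin or bleeding episode from any site will result in permanent discontinuation of PTX". That section allows dosing to continue where there is compelling evidence of another cause.

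Section 6.3.8.11 asks staff to "record on CRFs all values for hemoglobin, serum creatinine/calculated creatinine clearance, liver function tests", but gives no unit for hemoglobin. The schedule of events in Section 6.1 places hematology at screening and at every main study visit.

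Section 10.3.2.3 says what the entry criteria are for: "the eligibility criteria will reduce the potential adverse events associated with this drug by excluding those at higher risk".

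**The concern.** An eligibility criterion is applied, audited and cited in deviation reports by its text. Here the text gives a threshold on a scale 1000 times smaller than the one the protocol uses for the same measurement once the subject is on study. Both cannot be meant as printed.

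What is at stake is a safety screen. The protocol treats anemia and bleeding as possible during treatment: Section 7.3.1 requires that subjects be told about both, and the label material in Section 2.4 reports bleeding in treated patients. Section 10.3.2.3 then relies on the entry criteria to keep higher-risk subjects out. If the hemoglobin criterion has no effect as written, enrolling a severely anemic subject would not breach it.

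**Working it through.** The threshold is a stated criterion, not a derived figure, so the protocol has no calculation to reproduce here. The check is a unit conversion followed by a comparison of the two rules.

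**Inputs**
- Exclusion threshold: 9.0 mg/dL (Section 4.2).
- On-study rule: a fall of 2 gm/dL or more from baseline (Section 7.3.1).
- Conversion: 1 g = 1000 mg.

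**Step 1. Put both rules on one scale.**
- Section 4.2: 9.0 mg/dL / 1000 = 0.009 g/dL.
- Section 7.3.1: 2 gm/dL × 1000 = 2,000 mg/dL.

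**Step 2. Ask whether the two can coexist as printed.** A fall of 2 g/dL is possible only from a baseline of at least 2 g/dL. From the printed exclusion threshold it would leave 0.009 − 2 = −1.991 g/dL, which is impossible. So Section 7.3.1 presupposes baselines of 2 g/dL or more, and every such subject lies above 0.009 g/dL. On a literal reading the exclusion therefore removes no one. The protocol's own figures are enough to show this, without an outside reference range.

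**Step 3. Ask whether a unit slip alone would explain it.** If the same number is read in the unit of Section 7.3.1, a fall of 2 g/dL from it leaves 9.0 − 2 = 7.0 g/dL, which is a possible value. The two rules then fit on one scale. That makes a misprint the likely explanation. It does not establish that 9.0 is the intended number.

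**Step 4. Look for a correction elsewhere.** Section 6.3.8.11 names hemoglobin without a unit. The summary of chief exclusions in Section 10.2.1 does not mention hemoglobin. No section restates the threshold.

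**The case against.** The strongest reply is that this is a misprint with little practical effect. Section 9.6 says initial screening is done by the primary investigator with the research nurse coordinators. Section 7.3.1 shows that the protocol elsewhere uses gm/dL for hemoglobin, and people who work with that unit would probably read through the slip. This stands, and it is why the point is minor.

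Other provisions also limit the risk:
- Section 4.2 separately excludes bleeding diathesis, gastrointestinal ulceration or bleeding, cerebrovascular aneurysm or bleeding, and retinal hemorrhage, as well as aspirin, other NSAIDs and anticoagulants within 28 days before screening. Section 5.4.1 prohibits those drugs on study.
- Hematology is done at screening and at each main visit, and Sections 7.2 and 7.3.1 give on-study discontinuation rules.
- Section 10.2.3 puts the total blood volume at about 150 cc, and Section 10.3.2.2 describes the amount as well within donation standards.

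These stand too. They address bleeding history, interacting drugs and events after entry; none of them screens on low hemoglobin at entry.

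Three stronger readings are tempting, and the documents do not support them:
- **That anemic subjects will in practice be enrolled unchecked.** The literal reading excludes no one, but nothing shows that staff would apply 0.009 g/dL.
- **That the database would pass every subject.** Section 9.6 promises checks on data entry and warnings for outliers. It does not say that eligibility is programmed from the criterion text, and a plausibility check could equally well expose the mismatch.
- **That the protocol has no other hemoglobin rule, or that the fall in Section 7.3.1 being some 222 times the threshold (2,000 / 9.0) measures the problem.** Section 7.3.1 is itself a hemoglobin rule, though not one for eligibility. The ratio compares a change with a level; the relevant factor is the 1000 between the units.

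**Conclusion.** The point holds as a minor unit inconsistency in a criterion that is wrong as written. Its size is a factor of 1000 between the units of Sections 4.2 and 7.3.1.

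The conclusion that the exclusion has no effect rests on two assumptions: the text is applied literally, and subjects' hemoglobin values are on the scale that Section 7.3.1 presupposes. The first probably fails in practice, so the effect on enrolment is probably small. The documents give no figure from which to estimate it.

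Sample size, power and the primary analysis of FMD change are not affected. A reader might also infer that Section 7.3.1 settles the entry cut-off at the same number in gm/dL. It does not: that section governs a change during treatment, not a level at entry, and the intended criterion is for the sponsor to confirm.

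**What to change.** Reconcile the hemoglobin units in Sections 4.2 and 7.3.1. Ask the sponsor to confirm the intended exclusion criterion, both number and unit, without taking the on-study rule as deciding it. Carry the confirmed unit into the screening eligibility checklist. If a range or eligibility check for hemoglobin has been built into the database, confirm that it uses the same unit.

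The cost is one corrected line in the protocol and the matching entry on the checklist. No analysis or sample size text changes.

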PTX 400mg three times per day, was given to 9 subjects [128]. Two subjects were removed from study at weeks 2 and 5 due to initiation of prohibited concomitant drugs (inhaled steroid for bronchitis and cART for development of Kaposi Sarcoma, respectively) from their primary caregivers. FMD significantly improved after 4 weeks [median absolute increase 1.5%; p=0.04] and improved further at 8 weeks [median absolute increase from baseline 4.4%; p=0.02]. This degree of improvement in FMD has been associated with reduced risk of future cardiovascular events in the general population[21, 22]. Similar to what was observed with salsalate, 8 weeks of PTX resulted in normalization of FMD. Median NTGMD was 16% at entry and did not change over the course of the trial. It should be noted that the magnitude of improvement in FMD was similar regardless of initial FMD. . Looser stools were noticed by most of the subjects, but in none was this considered to be treatment-limiting. There were no drug-related laboratory toxicities.

We also observed in this pilot study a non-significant decline in triglycerides (p=0.09). No other lipid or metabolic parameter changed with PTX. Viral load did not change. Using an in-house HPLC assay, median plasma PTX concentrations were measured at weeks 4 and 8. The median PTX levels at weeks 4 and 8 were 73 ng/mL (270 nM) and 97 ng/mL (340 nM), respectively. There were no correlations between PTX concentrations and FMD response, which may reflect the small sample size of the study or that there is not a dose-response relationship between plasma PTX levels and FMD. We cannot rule out the possibility that intracellular levels of PTX may correlate with FMD response.

We examined the same peripheral blood markers of various potential inflammatory pathways as in the salsalate trial in order to gain insight into the pathways that may be responsible for the improvement in FMD with PTX. Because of the limited power in this pilot trial, we show in Table 1 those markers that we considered to have changed substantially, defined as either a change > 15% or a p-value < 0.05. Data are presented as median (range) due to small sample size.

Table 1. Markers of pathways that were affected by PTX.

| Biomarker* | Mechanistic Pathway | **HIV-infected Subjects Who Completed the 8 week trial of PTX (N=7)** | | |
| --- | --- | --- | --- | --- |
| Baseline  Median, pg/mL | % Change  (median) | P-value |

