6.2.2 Main Study Evaluations

There will be three main study visits where blood and urine samples will be obtained, anthropometrics performed, and brachial artery ultrasound measurements will be performed. The Week 4 visit will occur as near to Day 28 after entry as possible, but can occur as late as 42 days after entry. The Week 8 visit will occur as near to Day 56 after entry as possible, but can occur as late as 70 days after entry. Each subject will continue to take study drug/placebo until the final study visit is completed.

- - 1. Study Discontinuation Evaluations

Study subjects who complete the entry (Week 0/Day 0) procedures and have taken at least two weeks of study drug but thereafter notify the study team that they will terminate their involvement prior to the Week 4 visit will have their Week 4 evaluations performed as soon as possible after the time of notice of termination. Subjects who notify the study team that they will terminate their involvement prior to the Week 8 visit and have taken at least 6 weeks of study drug will have their study Week 8 evaluations performed as soon as possible after the time of notice of termination. Subjects who notify the study team that they will terminate their involvement within two weeks after the Week 0 or Week 4 visit evaluations have been completed will have no further evaluations performed.

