1. CRITERIA FOR STUDY DISCONTINUATION

- Request by the subject to withdraw
- Request of the primary care provider if s/he believes the study is no longer in the best interest of the subject
- If the subject is found to be pregnant or begins breastfeeding during the course of this study
- If the subject has develops fever, need for systemic therapy for acute or serious illness, or hypotension after screening that precludes completion of the main study visits within the allowed timeframes
- If the patient develops a need for antiretroviral therapy, as determined by the Principal Investigator or by the subject’s primary HIV caregiver
- Requirement for prohibited concomitant medication(s)
- Study drug-related toxicity (see section 7.0 Adverse Event Management)
- Clinical reasons believed life threatening by the physician
- Subject, as judged by the investigators, to be at risk of failing to comply with the provisions of the study protocol as to cause harm to self or interfere with the validity of the study results
- At the discretion of the funding agency

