#### 9.3.2 Primary Endpoint Analysis

#### The primary outcome is the change in FMD at week 8 of post treatment from baseline. An analysis of covariance (ANCOVA) model will be used to compare the effect of intervention on this outcome variable. The model will include an indicator variable for intervention, baseline FMD, and other potential covariates, including CD4 cell count, HIV-1 RNA level (viral load), age, sex, race, and BMI. We will include covariates one at a time while keeping the intervention and baseline FMD. All covariates except baseline FMD will be excluded from the model if they have insignificant association with the change in FMD. If the response variable does not follow a normal distribution, an appropriate transformation will be used to approximate a normal distribution. The assumption of the constant variance will also be tested, and a transformation will be used if this assumption is violated.

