9.3.3 Secondary endpoints analyses

The secondary endpoints are the change in FMD at week 4 and the changes in plasma levels of MCP-1, sVCAM-1, IP-10, fasting lipids, HOMA-IR, CD4 cell count, activated CD8 cell proportions, and HIV-1 RNA level at week 8 from baseline. The secondary analyses will be in exploratory nature and will primarily be used for hypothesis generation. All the secondary outcomes will be analyzed by the same statistical methods as for the primary endpoint. To analyze how the changes in secondary outcomes correlate with changes in FMD, Spearman Rank correlation will be used.

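### A Week 4 visit pushed past Day 42 by fever, illness therapy or low blood pressure ends participation, so the Week 8 primary FMD is not collected in its window (low priority, cheap to fix)

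*Combined protocol and SAP*

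**What the plan says.** Three notes in section 4.2 govern main study visits after entry. The note on therapy for acute infection or serious illness and the note on hypotension (systolic pressure below 90 mmHg) both end with "postponement outside of the allowed study visit timeframe will result in study discontinuation". The fever note ends with "fevers continuing past the allowed study visit timeframe will result in study discontinuation". The fourth bullet of the Criteria for Study Discontinuation (section 8) repeats the rule for any of these conditions "that precludes completion of the main study visits within the allowed timeframes".

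Section 6.2.2 defines three main visits: Weeks 0, 4 and 8. On timing it says "The Week 4 visit will occur as near to Day 28 after entry as possible, but can occur as late as 42 days", counted from entry. For Week 8 the window is Days 56-70.

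Section 9.3.2 states: "The primary outcome is the change in FMD at week 8 of post treatment from baseline". The model is an ANCOVA with baseline FMD. Section 9.3.3 begins its list with "The secondary endpoints are the change in FMD at week 4" and calls the secondary analyses exploratory.

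The Study Discontinuation Evaluations text in section 6.2 offers early Week 8 evaluations on a condition that reads "notify the study team that they will terminate their involvement prior to the Week 8 visit and have taken at least 6 weeks"; the weeks meant are weeks on treatment. Section 9.2 allows for 20% dropout and replaces subjects above that rate.

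**The concern.** The exit rule is attached to every main visit, but the primary analysis does not use every main visit. A randomized subject whose illness blocks Week 4 through Day 42 may be well again by Days 56-70 and able to give the primary measurement. As written, that subject is gone by then. Nothing exempts Week 4 or lets a subject miss it and return for Week 8.

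What is lost is a primary outcome that could have been collected from someone already randomized. Replacement under section 9.2 protects the head count but does not recover that subject's outcome.

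**Working it through.** **1. Timeline.** The Week 4 window closes on Day 42 and the Week 8 window opens on Day 56. A subject who exits on Day 43 leaves 56 - 43 = 13 days before the primary window opens.

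**2. How long the problem must last.** Let therapy start on Day S and run L days, and let the Week 4 visit first be attempted on Day A. The exit rule is triggered if S <= A and the last therapy day, S + L - 1, is at least 42. The shortest course that can do this is L = 42 - A + 1.
- A = 28: L = 15. A 14-day course never triggers it; a 21-day course does so only if started on Days 22-28.
- A = 35: L = 8. A = 38: L = 5.

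Later first attempts are plausible for some women, because section 3.3 schedules their visits by menstrual phase and section 10.7 expects about 25% women. Fever or low pressure must likewise block the visit to the end of the window. Because the fever note requires 48 afebrile hours, a fever on Day 41 already rules out Day 42.

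**3. Frequency.** The documents give no rate. In the two pilots (section 2.3.3), 11 - 2 = 9 salsalate and 9 - 1 = 8 PTX subjects remained at Week 4, 17 in all. No exit was attributed to this cause. For 0 of 17 the one-sided 95% upper limit is 1 - 0.05^(1/17) = 16.2%, or 0.162 x 26 = 4.2 subjects. The range is therefore 0 to about 4 of 26. It assumes that the pilots used a similar rule, which is not stated, and the upper end reflects the small denominator. Assumed rates of 2%, 5% and 10% give 0.5, 1.3 and 2.6 expected exits.

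**4. The plan's sample size (section 9.2).** SD of change = 2.21 x sqrt(2 x (1 - 0.30)) = 2.61 (stated as 2.62). With a difference of 3.5, a two-sided 5% t-test and 10 per group, noncentral-t power is 80.6%; with 9 per group it is 75.8%. Then 10/0.8 = 12.5, rounded up to 13 per group. The plan's figures reproduce.

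**5. Cost of one exit.** The plan's t-test uses SD 2.62. The planned ANCOVA on baseline FMD has residual SD 2.21 x sqrt(1 - 0.30^2) = 2.11, taking equal SDs at both times, balanced baselines and no other covariate.

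| Evaluable | t-test, SD 2.62 | ANCOVA, SD 2.11 |
|---|---|---|
| 13 + 13 | 90.4% | 98.2% |
| 13 + 12 | 89.2% | 97.7% |
| 10 + 10 | 80.6% | 93.8% |
| 10 + 9 | 78.2% | 92.4% |

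One exit costs 1.3 to 2.4 points on the t-test basis and about 0.4 to 1.4 points under the ANCOVA. Five dropouts of 26 (19.2%) fit the allowance; six (23.1%) trigger replacement.

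**6. The early evaluation.** A subject on drug through Day 42 has had six weeks of it. Even if the early-evaluation text is stretched to cover this exit, the scan falls before Day 56. The pilot reports that "FMD significantly improved after 4 weeks [median absolute increase 1.5%; p=0.04] and improved further at 8 weeks", where the median rise was 4.4%. An early scan could catch anything from 1.5% (no further rise yet) to 4.4% (plateau reached). That range spans the whole change between the two visits and rests on 7 completers, so the shortfall cannot be estimated.

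**The case against.** The strongest defence is that the rule is a deliberate choice. The protocol treats extrinsic inflammation as relevant to vascular outcomes (section 2.2.4) and bars infection therapy in the 14 days before screening. A subject ill through Day 42 may have a disturbed Week 8 FMD: a 21-day course from Day 25 ends on Day 45, 11 days before Day 56. This is a fair reason to book the scan late in its window. It is not a reason to lose a randomized subject's outcome under an intention-to-treat plan.

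A second point stands. A reader might infer that subjects leave merely because an exploratory scan was missed. The documents do not support that. The whole visit is postponed, and Week 4 also carries hematology, creatinine, liver tests, CD4 count, viral load and adverse event review. It is the only scheduled on-treatment safety visit before closeout, and the liver-test stopping rule (section 7.3.2) refers to it. Any fix must keep those assessments on time.

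Third, the early Week 8 evaluation may look like a rescue. It is worded for subjects who announce that they are stopping, not for exits that the protocol imposes, and it yields a scan outside the window.

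Finally, both PTX pilot exits followed prohibited drugs, so this change would have saved neither. That limits its value but does not remove the gap.

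**Conclusion.** The point holds as a low-priority improvement. Followed as written, the rule discards an in-window primary FMD that could often be collected. The event is probably rare, the cost per exit is small, and section 9.2 absorbs the likely number. The ANCOVA power figures rest on the plan's own SD of 2.21 and correlation of 0.30; the frequency range rests on the pilot assumption above.

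Three stronger readings are not supported:
- *A breach of intention to treat.* Section 9.1 governs how subjects are analysed, not which outcomes are collected. The rule sits awkwardly with that principle but does not contradict it.
- *Bias between arms.* Section 2.4.5 mentions small blood pressure decreases on pentoxifylline, so hypotension exits related to drug are possible. Nothing shows that they would differ by arm.
- *A threat to power.* Even one exit below 10 per group leaves 78.2% on the t-test basis and about 92.4% under the ANCOVA.

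**What to change.** In the three notes of section 4.2 and the fourth bullet of section 8, state that for these three triggers:
- a Week 4 FMD not done by Day 42 is recorded as missed;
- Week 4 safety laboratory tests and adverse event review are still completed by Day 42, without waiting for the scan;
- the subject stays in follow-up for the Week 8 FMD at Days 56-70, whether or not study drug continues;
- discontinuation for a missed window applies only to the Week 8 visit.

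Leave unchanged the requirement for systolic pressure of at least 90 mmHg on the morning of the scan, the drug-stopping rules of section 7 and the other section 8 criteria. No new rule for holding drug because of hypotension is needed for this purpose.

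The cost is wording in four places, with no new type of assessment and no change to the sample size. Some exploratory Week 4 FMD values will be missing, and affected subjects will have Week 4 blood drawn separately from a scan. Some Week 8 scans will follow soon after an illness; booking late in the window reduces this. In the 21-day example, Day 60 is 15 days after the last therapy day, beyond the 14 days used at screening.
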